**2.0 Trial Sponsor: None**

**3.0 Role of study sponsor/funders:** Funders played no role in design and conduct of the study; collection, management, analysis, and interpretation of the data; preparation, review, or approval of the protocol or related manuscripts.

**4.0 Composition of steering committee, data management teams:** The trial team managed trial data in partnership with Health Information Technology (HealthIT) at the trial location. The ongoing review of study data by the trial team ensured that the clinical study could continue without jeopardizing participant safety and the continuing validity and scientific merit of the trial. Because the study team had developed, validated, and analyzed the precise Electronic Health Record (EHR) data needed to conduct the trial, the team led on data and safety monitoring. The PI and study coordinator were responsible for monitoring the safety of participants, and for ensuring that participants are not exposed to undue risk.

## Study Schema

### 1.0 Background

Hospital Acquired Venous Thromboembolism (HA-VTE) remains the leading cause of death in hospitalized patients in the US. Approximately 900,000 people experience VTE each year, with incidence-based medical costs estimated between \$7 and \$10 billion per year. The second leading cause of disability-adjusted life-years, HA-VTE causes significant morbidity and mortality in adult and pediatric patients. Roughly 1 in 3 people experience long-term complications (i.e., post-thrombotic syndrome) following VTE. Reducing HA-VTE presents a major diagnostic challenge.

Despite numerous published prognostic models of HA-VTE, no single model outperforms the rest. And HA-VTE affects groups inequitably, which means models might reflect or worsen healthcare disparities if they are not deployed in the context of responsible, algorithmovigilant systems. Integrating scalable AI for HA-VTE prevention into effective clinical decision support (CDS) might effectively reduce HA-VTE incidence while aiding the realization of the potential for AI in high-value clinical practice. Recently, a Vanderbilt team of clinicians and biostatisticians validated a regression risk score called "VTE-AI" to prognosticate risk of HA-VTE on admission (DOI: [10.1016/j.rpth.2024.102433](https://doi.org/10.1016/j.rpth.2024.102433)).

The urban-rural divide has long caused healthcare disparities in morbidity and mortality. These differences might not result from rurality itself, but from "the effects of socio-economic disadvantage, ethnicity, poorer service availability, higher levels of personal risk and more hazardous environmental, occupational and transportation conditions." AI implementation will be no different without close attention to differences in both deployment settings. Studying multiple simultaneous implementations of AI in both urban and rural setting with adult and pediatric patients will yield unprecedented insights for AI-driven CDS.

### 2.0 Rationale and Specific Aims

This study will rigorously study *novel AI approaches* to this *important diagnostic challenge* and produce strong evidence for the pragmatic use of novel AI-CDS to prevent HA-VTE across diverse sites and populations.

The goal of this study is to evaluate the effectiveness of AI-driven CDS to reduce the incidence of HA-VTE across two dimensions: urban (Vanderbilt Adult Hospital [VUH]) and rural (Vanderbilt Regional Health System [VRHS] including Vanderbilt Tullahoma Harton Hospital [VTHH], Vanderbilt Bedford County Hospital [VBCH], and Vanderbilt Wilson County Hospital [VWCH]).

We will implement a validated risk score, VTE-AI, which does not require clinician input to calculate, to prompt CDS suggesting reconsideration of DVT prophylaxis in those who 1) do not have active prophylaxis ordered and 2) have no contraindication to pharmacologic prophylaxis. This CDS "nudge" will occur after admission orders have been submitted for hospital admissions and on each subsequent day of an inpatient encounter.

The current standard of care is an order set requiring manual calculation of the Padua risk tool and selection of a prophylaxis option or documentation of a temporary or permanent exception. We will evaluate the effectiveness of the VTE-AI-driven clinical

decision support (CDS) against the standard DVT/VTE prophylaxis order set to reduce HA-VTE incidence across urban/rural dimensions.

Aim 1: Prospectively validate the VTE-AI risk score in clinical production systems. We hypothesize the VTE-AI risk score will be non-inferior in clinical production compared to the retrospectively validated model (benchmark c-statistic > 0.8)

Aim 2: Develop a modified, simplified version of the DVT/VTE order set that does not require manual calculation of the Padua risk tool (standard of care) and assess its acceptability with clinicians in trial sites.

Aim 3: Conduct pragmatic RCT of VTE-AI-driven CDS against standard of care at VUH and VTHH. We will implement CDS at VUMC and VTHH randomizing half the eligible encounters to CDS and half to standard of care.

## 2.1 Objectives

### *Primary Objective*

We hypothesize CDS will reduce incidence of HAVTE in those i) predicted at high risk by VTEAI and ii) without evidence of pharmacologic prophylaxis in half, from baseline 4.3% incidence (562/12,946 events) to 2.2% incidence, which will require 2,236 encounters.

### *Secondary Objective*

We hypothesize the VTE-AI CDS will not increase bleeding risk, readmission rates, or lengths of stay (LOS) between the intervention and non-intervention arms.

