## 4.0 Inclusion/Exclusion Criteria and Study Setting

### Patient Inclusion Criteria

-Inpatient admission to VUH or VRHS (standard of care is all admitted patient encounters include the DVT/VTE prophylaxis order set as part of admitting orders)

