### *Eligibility Criteria*

All patients being admitted for inpatient care to VUMC Adult Hospital, Vanderbilt Tullahoma Harton Hospital, Vanderbilt Bedford County Hospital, or Vanderbilt Williamson County Hospital during its trial period.

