#### *Recruitment*

Because of the pragmatic nature of this RCT, enrollment/randomization occurs at the start of each encounter, when the VTE-AI risk score is calculated. No additional recruitment will be conducted.

---

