## **7.0 Risks**

This protocol presents minimal risks to participants. The risk model might identify risk in those not at high risk of HA-VTE, leading to pharmacologic prophylaxis that might not otherwise have been ordered. Adverse events include potential increased bleeding risk if prophylaxis is ordered from the CDS prompt that would not otherwise have been ordered. Bleeding from VTE prophylaxis in general is a rare event. The risk model is not perfect and might not identify risk in those who are at risk – it is not intended to preempt providers prophylaxing any patient (or all patients) for HA-VTE if they choose to do so.

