### *Auditing*

Study data will be analyzed by the PI and study team every three months for 1) continued validity of VTE-AI to prognosticate HA-VTE; 2) proper functioning of the VTE-AI model [e.g., ensuring all predictors continue to be calculated appropriately for patients]; 3) rates of HA-VTE and bleeding events. Because this study necessitates close collaboration with providers receiving BPAs, the study team will have monthly small-group virtual meetings with providers in study sites at VUMC to assess for problems or perceived AEs related to the study protocol, though none are anticipated.

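### Benefit is hypothesised in high-risk encounters without pharmacologic prophylaxis, but the no-harm objective is worded for arms that appear to contain all inpatients, which would dilute any bleeding the alert causes

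*Protocol*

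**What the plan says.** Population for benefit: section 2.1 (Primary Objective) places the expected halving of HA-VTE "in those i) predicted at high risk by VTEAI and ii) without evidence of pharmacologic prophylaxis". The Sample Size paragraph of section 6.0 and section 10.0 repeat this and derive 1,118 encounters per arm for that group.

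Population for harm: the Secondary Objective, directly below, hypothesises that the decision support "will not increase bleeding risk, readmission rates, or lengths of stay (LOS) between the intervention and non-intervention arms". It names no subgroup.

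Who is in the arms:
- Section 4.0 includes "Inpatient admission to VUH or VRHS" and lists no exclusions.
- Section 5.0 (Eligibility Criteria) opens with "All patients being admitted for inpatient care to VUMC Adult Hospital" and goes on to the regional hospitals.
- Section 6.0 (Recruitment) says that "enrollment/randomization occurs at the start of each encounter, when the VTE-AI risk score is calculated".

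Where harm can arise: section 6.0 (Intervention) lets the alert fire only when the score is above threshold, no pharmacologic order is active and no contraindication is documented. Section 7.0 identifies the hazard as "potential increased bleeding risk if prophylaxis is ordered from the CDS prompt that would not otherwise have been ordered".

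Section 6.0 (Secondary Outcomes/Endpoints) restricts neither bleeding nor length of stay to the high-risk group, and ties readmission to trial encounters. The three-monthly review in section 8.0 (Auditing) covers "rates of HA-VTE and bleeding events", again without restriction.

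**The concern.** Read as written, the two adjacent objectives answer questions about different patients. Benefit would be estimated where the alert can act. Harm would be estimated in a population where most encounters could never have triggered an alert. Adding unaffected encounters to both arms pulls the bleeding risk ratio towards 1 and the risk difference towards 0.

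The added sample size does not compensate. If the affected encounters are one in f of those randomised, the excess risk falls by f, while its standard error falls only by about the square root of f.

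Two things are at stake. A null whole-arm comparison could be taken as support for the no-harm hypothesis when the alert had raised bleeding in the patients it reached. And benefit and harm could not be weighed in the same patients, which is what a decision to keep the alert requires. The three-monthly bleeding review would be blunted in the same way.

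**Working it through.** **1. The plan's own figure.** Inputs (Protocol, Sample Size): 4.3% versus 2.2%, 80% power, 5% type I error, taken as two-sided. With p̄ = (0.043 + 0.022)/2 = 0.0325,

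n = [1.96·√(2p̄(1−p̄)) + 0.842·√(p₁(1−p₁) + p₂(1−p₂))]² / (p₁ − p₂)² = 1,118.1 per arm.

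Power at 1,118 per arm is 80.0%. The stated size reproduces, and it belongs to the restricted group.

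**2. Dilution factor f = all randomised encounters / encounters in the restricted group.** The Protocol gives no inpatient volume for the trial period, so f has to be assumed. The nearest figure is the validation cohort in section 6.0 (Prediction with VTE-AI): 132,365 encounters from 2018-2020.
- Spread over an assumed 36 months: 132,365/36 = 3,677 per month. Against the 150-230 qualifying encounters per month in the Sample Size paragraph, f = 3,677/150 = 24.5 down to 3,677/230 = 16.0.
- If instead the 12,946 encounters behind the baseline rate are the qualifying part of that cohort (also an assumption): f = 132,365/12,946 = 10.2.

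The range is therefore about 10 to 25. The square root of f is 3.2 at f = 10 and 5.0 at f = 25, which is the approximate factor by which the z-statistic falls.

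**3. Effect on the bleeding comparison.** The Protocol gives no bleeding rate. Assume a background rate p₀, equal inside and outside the restricted group, multiplied by RR in the restricted group of the alert arm. Over whole arms, n = 1,118·f per arm and p₁ = p₀ + p₀(RR − 1)/f. With d = p₁ − p₀,

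power = Φ((d − 1.96·se₀)/se₁) + Φ((−d − 1.96·se₀)/se₁),

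where se₀ = √(2p̄(1−p̄)/n), with p̄ now the mean of p₀ and p₁, and se₁ = √((p₀(1−p₀) + p₁(1−p₁))/n).

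For 1% doubled:
- Restricted group: d = 0.0100, both standard errors 0.00514, power Φ(−0.01) = 49%.
- f = 10: n = 11,180, d = 0.0010, standard errors 0.00136, power 11%.
- f = 20: n = 22,360, d = 0.0005, standard errors 0.00095, power 8%.

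| Assumed bleeding | Restricted, 1,118 per arm | Whole arms, f = 10 | Whole arms, f = 20 | Whole arms, f = 24.5 |
|---|---|---|---|---|
| 1% doubled | 49% | 11% | 8% | 8% |
| 1% tripled | 92% | 30% | 18% | 16% |
| 2% doubled | 79% | 18% | 12% | 10% |
| 3% tripled | about 100% | 71% | 44% | 38% |

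**4. How it would look in a report.** For 1% doubled at f = 20, the expected whole-arm risk ratio is 1.05. On the log scale its standard error is √((1−p₀)/(n·p₀) + (1−p₁)/(n·p₁)) = 0.093, so the 95% interval is about 0.88 to 1.26. The true ratio in the patients reached would be 2.0.

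**The case against.** **The arms may not be all inpatients.** The Secondary Objective speaks of arms and never says all inpatients. The Sample Size paragraph uses the word arm for the 1,118 high-risk, unprophylaxed encounters and sets the trial's length from the monthly count of such encounters. Aim 3 in section 2.0 randomises eligible encounters. On that reading both objectives share one population and nothing is diluted. This stands as a possible reading, but it is the weaker one: section 5.0 defines eligibility as all admitted patients, and randomisation is placed at the start of the encounter. No section applies the restriction to the secondary outcomes.

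**Benefit and harm are treated alike elsewhere.** The Primary Outcome in section 6.0 is as unrestricted as the secondary outcomes, and the audit lists HA-VTE and bleeding together. That is correct. The mismatch lies between the hypothesis sentences, and the analysis set for safety may be settled in a statistical analysis plan that is not at hand. The point is therefore about what the Protocol's wording fixes, not about a missing method.

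**The size is uncertain.** A reader might infer a 20-fold dilution and a no-harm conclusion that is close to assured. The documents support neither. The factor rests on a proxy cohort from other years, which may not represent all admissions or the trial hospitals. No bleeding rate or no-harm decision rule is stated, and the power figures matter only if a non-significant difference is read as no harm. A tripling from 3% would still be detected 44% of the time at f = 20.

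**The restricted comparison is not strong either.** At 49% power for a doubling from 1%, a null result there would also be weak evidence of safety. Nor does that group match the alert's reach exactly, because the alert also requires that no contraindication be documented.

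**Conclusion.** The concern holds in a limited form. The Protocol ties benefit to a subgroup and words the no-harm objective for arms that, on its eligibility and randomisation text, contain all inpatient admissions. On that reading, bleeding caused by the alert is diluted by a factor the Protocol does not give, about 10 to 25 under the proxy volumes used here. For a doubling from an assumed 1%, the chance of missing it rises from about 51% in the restricted group to about 89-92% over whole arms.

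These figures assume equal background bleeding inside and outside the restricted group and a two-sided 5% test. Harm would probably be missed, but a null result is not guaranteed. The primary sample size is unaffected.

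**What to change.** - In the Secondary Objective (2.1) and Secondary Outcomes/Endpoints (6.0), state that bleeding, readmission and length of stay are compared between arms in the population of the primary hypothesis, with membership determined identically in both arms from data recorded before any alert. Report the same comparisons over all randomised encounters as well.
- In Auditing (8.0), show the three-monthly bleeding rate in that population too.
- Reconcile sections 2.0 (Aim 3), 2.1, 4.0, 5.0 and 6.0 (Primary Outcome, Secondary Outcomes, Sample Size, Recruitment) on who forms the arms. Say whether the absence of a documented contraindication, which the alert requires, is part of the population definition.

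The cost is wording. The data come from the same record queries and no extra patients are needed. The downside is wider safety intervals in the restricted population, so the report should give the interval and not rest on non-significance.

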## 3.0 Animal Studies and Previous Human Studies

No animal or human studies have been done.

## 4.0 Inclusion/Exclusion Criteria and Study Setting

### Patient Inclusion Criteria

-Inpatient admission to VUH or VRHS (standard of care is all admitted patient encounters include the DVT/VTE prophylaxis order set as part of admitting orders)

### Patient Exclusion Criteria

-None

### *Study Setting*

The study is conducted at Vanderbilt University Medical Center (VUMC), an academic medical center in the Mid-South of the United States. Within VUMC, the trial is conducted in VUH, the main urban adult hospital in Nashville, and VRHS, a collection of hospitals including a rural hospital in Tullahoma, Coffee County, TN.

## **5.0 Enrollment/Randomization**

Randomization will be done in the Epic EHR, built-in functionality. One half will be randomized to VTE-AI-driven CDS and one-half to standard of care.

### *Eligibility Criteria*

All patients being admitted for inpatient care to VUMC Adult Hospital, Vanderbilt Tullahoma Harton Hospital, Vanderbilt Bedford County Hospital, or Vanderbilt Williamson County Hospital during its trial period.

## **6.0 Study Procedures**

### *Prediction with VTE-AI*

VTE-AI uses a prognostic model of HA-VTE validated on 132,365 adult patient encounters from 2018-2020. The model uses 39 factors selected from a diverse candidate list of 84 risk factors ranging from demographic and clinical characteristics, diagnostic procedures, vital signs, and laboratory measurements (e.g., complete blood counts, chemistry panels). All predictors are routinely collected and available for prognostic calculation in real-time, such as insertion of a central venous catheter ( $c^2$ : 192.1), history of cardiac arrhythmia ( $c^2$ : 175.8), recent weight loss ( $c^2$ : 96.2), admission source ( $c^2$ : 77.8), and C-reactive protein ( $c^2$ : 43.1). This model has performed with good to excellent discriminative ability thus far (c-statistics 0.89-0.9).

This model is a statistical risk model using logistic regression, which means the variables above are used in a mathematical equation to estimate a probability that HA-VTE will occur for that individual in the future.

### *Randomization*

Randomization will occur using Epic EHR's randomization feature, built into the EHR.

### *Primary Outcome/Endpoint*

Incidence of HA-VTE, VTE associated with healthcare encounter. We will exclude VTE present on admission (VTE-POA) as a study outcome.

### *Secondary Outcomes/Endpoints*

Secondary trial outcomes include process metrics – Length of Stay, Readmission Rates – and safety metrics – bleeding events. Length of Stay is measured as days between admission and discharge. Readmission Rates will be rates of readmission within 30-days of discharge for trial encounters related to VTE. Bleeding events are a safety risk from anticoagulation and DVT/VTE prophylaxis and will be monitored during the trial.

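### All-cause death is not an outcome and length of stay ignores discharge status, so a difference in in-hospital deaths between arms could go unreported

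*Protocol*

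**What the plan says.** - **No-harm hypothesis** (Protocol 2.1, Secondary Objective): the CDS "will not increase bleeding risk, readmission rates, or lengths of stay (LOS") in the comparison of arms.
- **Secondary outcomes** (Protocol 6.0, Secondary Outcomes/Endpoints): "Secondary trial outcomes include process metrics – Length of Stay, Readmission Rates – and safety metrics – bleeding events". LOS is defined there as: "Length of Stay is measured as days between admission and discharge". Readmission is defined as: "Readmission Rates will be rates of readmission within 30-days of discharge for trial encounters related to VTE". Neither definition mentions whether the patient was discharged alive.
- **Primary outcome** (Protocol 6.0, Primary Outcome/Endpoint): "Incidence of HA-VTE, VTE associated with healthcare encounter", leaving out VTE already present on admission. Death is not a component.
- **Three-monthly review** (Protocol 8.0, Auditing): apart from model validity and function, the item reviewed is "3) rates of HA-VTE and bleeding events". Deaths are not named.
- **Background** (Protocol 1.0): HA-VTE "remains the leading cause of death in hospitalized patients in the US". The protocol thus presents the disease as a cause of death but does not plan to count deaths.

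**The concern.** LOS and readmission are used as evidence that the alert does no harm, yet death ends both. A stay that ends in death has a length under the stated definition and is averaged with stays that end in recovery. A patient who dies in hospital cannot be readmitted. Encounters are flagged as high risk and there are no exclusion criteria, so some in-hospital deaths are to be expected.

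If deaths differed between arms and were not recognised as bleeding or HA-VTE, no listed outcome would count them. The trial could then report no increase on its three no-harm outcomes without the reader learning that mortality differed.

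**Working it through.** **1. The plan's own figure, for scale.** Inputs from the Sample Size section: 4.3% against 2.2%, 80% power, 5% type I error. Taking a two-sided test with pooled variance and no continuity correction:

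n = [1.960 × √(2 × 0.0325 × 0.9675) + 0.842 × √(0.043 × 0.957 + 0.022 × 0.978)]² / 0.021² = (0.4915 + 0.2107)² / 0.000441 ≈ 1,118.1, or 1,119 when rounded up.

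The stated 1,118 per arm is reproduced. The hypothesised benefit is 1,118 × 0.021 ≈ 23 HA-VTE events avoided. The point made here does not depend on the sample size.

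**2. Where a death could be counted.**
- A recognised fatal bleed can be counted as a bleeding event.
- A recognised fatal embolism can be counted as HA-VTE.
- A death recognised as neither is counted in no listed outcome. It still enters LOS. It enters the readmission rate as a non-readmission if the denominator is all trial encounters, which the protocol does not settle.

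**3. Effect on LOS.** The protocol gives no mortality or LOS figures, so these inputs are assumptions: mean stay of survivors L = 6 days, mean stay of those who die d = 2 to 14 days, in-hospital mortality m of 3% against 4%, 4% against 6%, or 4% against 8%.

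Mean LOS = (1 − m) × L + m × d, so the difference between arms is Δm × (d − L).

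| d (days) | Δm = 1 point | Δm = 2 points | Δm = 4 points |
|---|---|---|---|
| 2 | -0.04 | -0.08 | -0.16 |
| 4 | -0.02 | -0.04 | -0.08 |
| 6 | 0.00 | 0.00 | 0.00 |
| 10 | +0.04 | +0.08 | +0.16 |
| 14 | +0.08 | +0.16 | +0.32 |

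The sign is that of d − L: early deaths shorten mean LOS and late deaths lengthen it. The extra deaths per 1,118 encounters are about 11, 22 and 45.

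**4. Effect on readmission.** If those who die stay in the denominator, the rate is r × (1 − m) and the difference is −r × Δm. With an assumed r = 10% among those discharged alive, it is -0.1, -0.2 and -0.4 percentage point. Only VTE-related readmissions count, so r is probably lower. With r = 2% and Δm = 2 points the shift is -0.04 point. If the denominator is live discharges, this effect disappears.

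**5. Would the listed outcomes show the deaths?** With an assumed LOS standard deviation of 5 to 8 days, the standard error of the LOS difference is SD × √(2/1,118) = 0.21 to 0.34 day. Every 2-point shift in the table is smaller than one standard error. A direct comparison of 4% with 6% has standard error √[(0.04 × 0.96 + 0.06 × 0.94)/1,118] = 0.92 point, so the same 2-point difference is about 2.2 standard errors. LOS barely registers a mortality difference that a direct count would be likely to show.

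**The case against.** The strongest case on the other side has four parts.

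- **The bias is small and its direction is not fixed.** This stands. The LOS shift can be negative, zero or positive, and at a 2-point mortality difference it lies within sampling error. The readmission shift is a fraction of a point and may not arise at all. An effect on HA-VTE through lost time at risk would also be slight: if the extra deaths carried average risk and lost all their time at risk, 4.3% × 2 points ≈ 0.09 point, against a planned 2.1.
- **Bleeding, the harm the protocol identifies, is measured.** This stands too. Bleeding is compared between arms and reviewed every three months, so a reader who infers that no listed outcome could reveal a fatal harm goes too far. The gap is deaths not recognised as bleeding or HA-VTE.
- **Adverse-event reporting would catch deaths.** Only in part. Protocol 8.0 calls for prompt reporting of events that are unexpected and at least possibly related to the research, and leaves other adverse events to continuing review. Neither is a comparison of deaths by arm, and a death put down to underlying illness may not be linked to an alert.
- **The handling of deaths belongs in a SAP, which is not shown.** This holds for modelling detail. It does not hold for the choice of outcomes or for the LOS definition, both of which the protocol fixes. Admission to discharge is a conventional measure and contradicts nothing else in the protocol. The weakness lies in using it as no-harm evidence without mortality beside it.

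**Conclusion.** The concern holds as an omission from the outcome list, made worse by an LOS definition that does not separate death from recovery. All-cause death is absent from the primary outcome, the secondary outcomes, the no-harm objective and the three-monthly review. At an assumed 2-point mortality difference, about 22 extra deaths in one arm could go unreported in the comparison of arms, if not recognised as bleeding or HA-VTE. That is close to the 23 HA-VTE events the trial hopes to avoid. The mortality figures are illustrative, and nothing in the protocol suggests that such a difference is likely.

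A reader might infer that any in-hospital death scores as a short stay with no readmission, so that harm would appear as benefit. The protocol does not support that. It gives no timing of deaths, late deaths push LOS the other way, and the readmission effect depends on a denominator that is not stated. The supportable conclusion is that LOS becomes hard to interpret, readmission may fall slightly, and the deaths themselves are not counted.

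**What to change.** 1. Add all-cause in-hospital death by arm as a safety outcome, taken from discharge disposition in the EHR, and include it in the three-monthly review under Auditing.
2. Define LOS as time to live discharge with in-hospital death as a competing event, and report it alongside mortality.
3. Use encounters discharged alive as the readmission denominator.

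The definitions belong in the protocol; the modelling detail can sit in the SAP. Because outcomes change, the amendment should follow the route in Protocol 13.0, including the registry update, and is best made before outcomes are compared by arm. The cost is minor extra EHR extraction and analysis. No patients, visits or procedures are added, and the sample size stays the same.
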